## Abstract

**Background:** Stroke is a major cause of death and disability worldwide. The related burden is expected to further increase due to aging populations, calling for more efficient treatment. Ischemic stroke results from a focal reduction in cerebral blood flow due to the sudden occlusion of a brain artery. Ischemic brain injury results from a sequence of pathophysiological events that evolve over time and space. This cascade includes excitotoxicity and peri-infarct depolarizations (PIDs). Focal impairment of cerebral blood flow restricts the delivery of energetics substrates and impairs ionic gradients. Membrane potential is eventually lost, and neurons depolarize. Although recanalization therapies target the ischemic penumbra, they can only rescue the penumbra still present at the time of reperfusion. A promising novel approach is to “freeze” the penumbra until reperfusion occurs. Transcranial direct current stimulation (tDCS) is a non-invasive method of neuromodulation. Based on preclinical evidence, we propose to test the penumbra freezing concept in a clinical phase IIa trial assessing whether cathodal tDCS—shown in rodents to reduce infarction volume—prevents early infarct growth in human acute Middle Cerebral Artery (MCA) stroke, in adjunction to conventional revascularization methods.

**Methods:** This is a monocentric randomized, double-blind, and placebo-controlled trial performed in patients with acute MCA stroke eligible to revascularization procedures. Primary outcome is infarct volume growth on diffusion weighted imaging (DWI) at day 1 relative to baseline. Secondary outcomes include safety and clinical efficacy.

**Significance:** Results from this clinical trial are expected to provide rationale for a phase III study.

**Clinical trial registration**—EUDRACT: 2016-A00160-51

## Introduction

Ischemic stroke is a main etiology of death or severe disability. It affects over 13.5 million of people worldwide annually. Ischemic stroke results from a focal reduction in cerebral blood flow due to the sudden occlusion of a brain artery. In the first hours after ischemic stroke brain imaging can distinguish an ischemic core (necrosis of neurons) and a penumbral area where hypoperfusion is mild to moderate. Neurologic disability is the consequence of both the ischemic core and the penumbra. In the penumbra, with energy depletion, membrane potential is eventually lost, neurons and glia depolarize, and cell necrosis ensues. Current opportunities to salvage the ischemic penumbra are based on early recanalization of the occluded artery allowing early reperfusion of ischemic tissue. Three strategies are available: IV thrombolysis with recombinant tissue plasminogen activator (rtPA), endovascular thrombectomy (EVT), or the combination of IV thrombolysis and EVT (1–9). However, despite these procedures, only 46% of patients have mild disability at 3 months (10). To improve functional outcome, numerous neuroprotective strategies appeared promising in preclinical models. However, so far they have failed in clinical trials (11, 12).

A promising novel strategy for neuroprotection is to “freeze” the ischemic penumbra until reperfusion occurs (i.e., prevent further demise of the penumbra until reperfusion) (13). Among the factors that may affect the course of the penumbra, Leão in 1947 first described cortical spreading depression (CSD) characterized by a spreading depolarization of neurons and glial cells associated with ion homeostasis breakdown (14). In stroke, CSDs propagate as peri-infarct depolarizations (PIDs) across the cerebral cortex from the ischemic core to the penumbra, and are associated with infarct growth (15–17).

Transcranial direct current stimulation (tDCS) is a non-invasive brain neuromodulation technique that uses direct electrical currents to stimulate specific parts of the brain. A constant, low intensity current is passed through two electrodes placed over the head, which modulates neuronal activity. Polarizing currents are produced and able to cross the skull and induce sustained changes in membrane potential and excitability of cortical cells. tDCS may affect neuronal and glial transmembrane potential (18–20). The widespread opinion is that cathodal tDCS reduces cortical excitability whereas anodal stimulation increases it (by hyperpolarization and depolarization, respectively) (21). Cathodal tDCS blocked CSD initiation in a rat model where CSDs are elicited by pricking the cortex with a needle (22). Moreover, three studies in ischemic stroke rodent models demonstrated a neuroprotective effect of cathodal tDCS with a significantly reduced infarct size relative to controls (see section Discussion for details) (23–25). Only a few tDCS studies have been conducted in humans at the early stage of MCA stroke. However, these studies were performed with a different objective: to promote early motor recovery, using anodal tDCS stimulation facing the stroke area (26–29). In these studies, no adverse effect was described.

Based on preclinical studies, we hypothesized that, probably via blocking CSDs and PIDs, cathodal tDCS may limit infarct growth in human acute MCA stroke.

We present here the design of the STICA trial: “tDCS in acute human ischemic stroke, a pilot, prospective, double-blind, placebo-controlled randomized clinical trial.”

## Study design and methods

### Subjects eligibility, ethical considerations, and recruitment

#### Inclusion and exclusion criteria

Initial inclusion criteria were adult patients (age over 18 years-old) with acute ischemic stroke in MCA territory (no lacunar stroke) proved by MRI; with time from stroke onset to treatment minor than 4:30 h; National Institutes of Health Stroke Scale (NIHSS) between 4 and 25; and eligible to receive IV thrombolysis with rtPA. Two amendments were subsequently adopted in order to include all patients with acute ischemic stroke in the MCA territory eligible to a revascularization procedure (irrespective of the revascularization procedure—IV thrombolysis and/or EVT—and irrespective of the NIHSS score). Exclusion criteria are contraindications to MRI, forehead skin injuries, history of intracranial surgery (because it implies skull breach which could modify tDCS current distribution), consciousness impairment (in order to uniformly assess tDCS safety between participants), and pregnancy “known at the patient's admission” (for ethical considerations).

#### Ethical considerations and dissemination

All patients provide written informed consent in accordance with the Declaration of Helsinki before inclusion in this study if they can provide it. Otherwise, their relatives are asked for consent. If no relative is available, the patient can be included using an “emergency procedure.” If consent is given by relatives or if the patient is included using the “emergency procedure,” a complementary consent has to be completed by the patient as soon as possible. The study protocol was approved by the local ethics committee (2016-A00160-51, ref CPP 3373) and registered at EUDRACT: 2016-A00160-51.

The STICA protocol is intended to evaluate the potential of cathodal tDCS to limit ischemic damage in acute human MCA stroke, as an adjunct to standard-of-care revascularization strategies. The results from this study will be disseminated to healthcare professionals via publication in a peer-reviewed journal. Moreover, we intend to present the findings in international stroke, neurophysiology, and neuromodulation conferences.

### Trial design, randomization and intervention

#### Trial design

Our study is an ongoing monocentric prospective double-blind and placebo-controlled clinical phase IIa trial with randomized treatment-group allocation, according to CONSORT statements (30). tDCS plus usual care (thrombolysis ± thrombectomy) is compared to sham-tDCS plus usual care (control group) in patients with acute MCA stroke. Patients are being recruited in Sainte Anne's hospital Stroke unit since December 2016. Complete recruitment is expected in June 2019.

In our institution, endovascular treatment is considered in acute middle cerebral artery (MCA) stroke in the following situations: if time of stroke onset is <6 h, and if there is a “proximal” arterial occlusion (internal carotid, M1 and proximal section of part M2 of MCA). Until the 27th of June 2018, endovascular treatment was not used if time of stroke onset was beyond 6 h. Since this date, if last-seen-well time is between 6 and 24 h, endovascular treatment is performed if the patient meets the criteria of the DEFUSE 3 or DAWN trial criteria (31, 32).

All subjects undergo MRI scanning at baseline, just before enrollment. MRI protocol includes Diffusion Weighted Imaging (DWI), Fluid Attenuated Inversion Recovery (FLAIR), 3D-Time-Of-Flight imaging, and Perfusion-Weighted-Imaging (PWI) whenever possible. PWI was not included routinely because it is not required to assess the primary outcome of our study. Moreover, some severely affected patients with hyper-acute stroke or speech disturbances can be agitated or unstable and the MR exam occasionally has to be interrupted before PWI acquisition. If they meet inclusion criteria, subjects are randomized to receive either cathodal or sham tDCS in adjunction to a recanalization procedure, in a complete double-blind fashion. All participants undergo a second MRI scanning at day 1 (with DWI for primary outcome assessment) and clinical examination at day 7 (or discharge if earlier). Follow-up is obtained at 3 months by phone interview by one investigator (blinded to randomization) in order to assess the modified Rankin Scale (33).

#### Randomization

All patients are randomly assigned to receive either cathodal or sham-tDCS. The randomization list was previously established with a biostatistician (using the block method), allocating a different 5-digit code to each patient included, in a sealed envelope. All five-digit codes are pre-programmed into the tDCS device to deliver either active or sham tDCS and the randomization list was transmitted to the biostatistician to maintain the blinding of all experimenters. At the time of inclusion, just after the MRI scanning and before revascularization treatment whenever possible (otherwise, during the revascularization procedure), the experimenter opens the sealed envelope corresponding to the number of the patient being included and discovers its 5-digit code.

#### Intervention

The intervention consists in cathodal tDCS by the DC-STIMULATOR PLUS (neuroConn, Ilmenau, Germany), a CE-certified medical device, programmed to deliver either active or sham-tDCS according to a randomization 5-digit code. tDCS or sham is started as soon as possible after the inclusion, in the stroke unit or in the angiosuite during thrombectomy, in addition to reperfusion therapies. The investigator sets the cathode facing the ischemic injury (C3 or C4 according to the 10–20 system) and the anode facing the contralateral supra-orbital area (Figure 1). Then, the experimenter enters the 5-digit randomization code in the device, which blindly determines whether cathodal or sham stimulation is to be delivered, without the experimenter knowing which. Delivery of stimulation is for 20 min. Over a period of 6 h, the experimenter restarts the device every hour with the same 5-digit randomization code for another 20 min. The device delivers 1.5 mA (with 30 s for ramping up and ramping down) of cathodal direct current through the two sponge coated electrodes (electrodes size: 5 × 7 cm^2^; Figure 2). Impedance quality is obtained using saline solution and conductive gel (Elefix paste®). The device automatically checks impedance values during all tDCS sessions. In the sham condition, the device delivers 98 s of current including 30 s for ramping at the beginning and end of each session, in order to keep the blinding procedure (Figure 3). Indeed, usually, subjects feel discomfort under the electrodes during only the first few seconds or minutes of tDCS stimulation (18, 34). The experimenter notes every significant event: time of stroke onset, time of hospital arrival, time of first MRI, time of IV thrombolysis, and/or endovascular recanalization, time of each tDCS session (Figure 4).

**Figure 1 F1:**
[figure not shown]
Study design.

**Figure 2 F2:**
[figure not shown]
tDCS device and tDCS electrode positioning. In case of left MCA stroke, in order to hyperpolarize the ischemic penumbra, the cathode (in blue) faces the ischemic injury (C3, 10–20 system) and the anode (in red) faces the contralateral supra-orbitary area.

**Figure 3 F3:**
[figure not shown]
Timelines of active tDCS (left) and sham tDCS (right), and treatment protocol.

**Figure 4 F4:**
[figure not shown]
Timeline of procedures. IA, intra-arterial; IV, intravenous.

### Safety aspects

During the procedure, potential tDCS adverse events are checked every hour: itching, irritation, or rash, burning feelings under the electrodes, headaches, nausea, and dizziness. All these minor side events are reversible when the tDCS stops (35). To minimize these risks, a dedicated experimenter is present during each tDCS stimulation session. This experimenter asks the patient about any side-effect or discomfort and notes these data each hour. The tDCS procedure is stopped in case of adverse events.

In order to minimize the risk of rash or burning feelings, the experimenter adds saline solution and conductive gel (Elefix® paste) every hour if necessary, according to impedance values. High impedances are indeed a contributing factor for skin lesions (35). Moreover, the device automatically stops in case of impedance value superior to 15 kΩ. An independent data and safety monitoring board analyzes STICA safety data after the recruitment of 25 patients.

### Outcomes

#### Primary outcome

The primary outcome is infarct growth (IG, in mm) determined using the MRI obtained at admission (DWI_1_) and 1 day later (DWI_2_). This analysis is performed voxel-wise. In this method, infarct growth corresponds to the volume of signal changes on DWI_2_ that does not overlap with that on co-registered DWI_1_ (36).

An automated three-dimensional rigid registration is used for MR images processing (FMRIB's Linear Image Registration Tool; FLIRT, V5.5) (37). Follow-up (24 h) DWI images are co-registered to pre-treatment DWI images, chosen as the target space. Registration quality is visually inspected for all cases. DWI lesions are segmented manually using our published methods (36, 38–40), based on DWI signal intensity (MANGO software, V3.1.1, Research imaging Institute, UTHSCSA). Initial and follow-up DWI lesions are outlined according to their maximal visual extent after careful adjustment of the window level. Segmented DWI lesions are transferred onto Apparent Diffusion Coefficient (ADC) maps to exclude any areas of T2 shine-through effect, and include areas of decreased ADC with subtle DWI signal changes. Segmented follow-up DWI lesions are transferred onto pre-treatment DWI maps to ensure a full coverage of brain tissue.

Infarct growth is also systematically estimated using the subtraction method, as ancillary assessment: in this method, the baseline DWI lesion volume is simply subtracted from the DWI lesion volume measured on follow-up MRI. All imaging data are analyzed by a neuroradiologist unaware of treatment-group assignment.

#### Secondary outcomes

We defined two secondary clinical outcomes, a safety outcome and three subgroups analyses.

NIHSS: a neurological exam (with NIHSS score) is assessed at the admission and at 7 days or discharge if earlier. The difference between NIHSS score at day 7 (or discharge if earlier) and on admission constitutes the first clinical outcome assessment.Modified Rankin scale (mRs): the mRs is a 7-point disability scale ranging from 0 (no symptom) to 6 (death).The mRs is estimated at 3 months by phone interview using a simplified and standardized questionnaire (33). Whenever possible, the patient will be interviewed directly. If the patient is unable to complete the interview, the interview will be conducted based on information from the relatives or the patient's general practitioner. The mRs at 3 months constitutes the second clinical outcome assessment.

Safety outcome: safety variables, including major adverse effects (neurologic deterioration) and minor adverse effects (itching sensations, cutaneous rash, headaches, vertigo, nausea) are monitored during tDCS stimulation, and then again at day 1 and day 2.Subgroup analyses are planned according to the following stratifications: (i) patients with and without perfusion–diffusion mismatch, with hypoperfusion defined as *T*_max_ > 6 s, on admission MRI. The perfusion–diffusion mismatch is defined by the volumetric ratio between perfusion lesion (at *T*_max_ > 6 s) and diffusion lesion (ratio > 1.8). The mismatch as defined is a neuroradiological marker of the ischemic penumbra, the target of our protocol; (ii) patients with NIHSS admission score above vs. below the median NIHSS admission score; (iii) presence or absence of arterial recanalization measured by the thrombolysis in cerebral infarction scale (TICI) post-arteriography or by MR Angiography at day 1 (successful recanalization on arteriography is estimated by a TICI scale 2b or 3) and (iv) patients with and without initial large vessel occlusion. The patient population will be clearly described with respect to vessel occlusion (no vessel occlusion, otherwise site of occlusion) in further publication.

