### Statistical analysis

Continuous variables are described as mean ± standard deviation (SD) or median [interquartile range (IQR)] and are compared using the *t*-test or Mann-Whitney U-test. Categorical variables are expressed as percentages and compared using the Pearson χ^2^-test or Fisher's exact test, as appropriate. A univariate analysis is expected and adjustment is scheduled according to the success or not of recanalization. Primary outcome is analyzed in intention-to-treat, safety outcomes in per-protocol.

No intermediate analysis is planned. All data for the primary outcome will be assessed at the end of the study. The inclusion of 50 patients is planned over 30 months. This sample will allow to evaluate the feasibility of tDCS in the very acute phase of stroke and should highlight a tendency which will be used in further studies to demonstrate a statistically significant infarct growth difference between the two groups.

The number of patients (*n* = 25 per group) was empirically chosen to match the recruitment capacity of our center during the study period, and because we believe it would provide a reliable estimate of the effect size of the intervention for further studies. This planned number of patients was not based on a formal sample size calculation and we are aware that the present pilot trial will most likely be underpowered to demonstrate the superiority of the intervention over the control group with regard to the primary outcome.

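### The first clinical outcome compares raw NIHSS change between groups without using admission NIHSS as a covariate, which generally loses precision

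*Protocol article*

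**What the plan says.** The Secondary outcomes section of the Protocol article sets the measurement times: "a neurological exam (with NIHSS score) is assessed at the admission and at 7 days or discharge if earlier". It then defines the outcome as the raw difference: "The difference between NIHSS score at day 7 (or discharge if earlier) and on admission constitutes the first clinical outcome assessment".

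The Statistical analysis section compares continuous variables with a two-sample t-test or a Mann-Whitney U-test. On adjustment it says: "A univariate analysis is expected and adjustment is scheduled according to the success or not of recanalization". Recanalization is judged on arteriography or on day-1 MR angiography, so it is a post-randomization factor.

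Admission NIHSS enters the planned analyses in one other place, as a subgroup factor: "patients with NIHSS admission score above vs. below the median NIHSS admission score". It is not named as a covariate.

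On eligibility, the original NIHSS limits of 4 to 25 were lifted by amendment, and patients now enter "irrespective of the NIHSS score". The Randomization section describes blocks and states no stratification factor. The planned size is 25 per group.

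On death, the mRS has its own level (6). The NIHSS difference has no counterpart for a patient who dies before the assessment. The analysis sets are given as "Primary outcome is analyzed in intention-to-treat, safety outcomes in per-protocol"; none is named for the clinical outcomes.

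**The concern.** How far a patient can improve depends on where that patient starts. Someone admitted at 2 can gain at most 2 points, someone admitted at 20 can gain 20. Part of the spread in the change score is therefore predictable from the admission score, and a two-sample test treats that part as noise. With 25 per group and no stated stratification, the groups may also differ by chance in admission NIHSS, and subtracting the baseline removes that difference fully only if day-7 NIHSS rises by one point for each admission point.

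Adjusting for recanalization does not make up for this. It is not a baseline variable and does not stand in for the admission score.

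A second, smaller matter is that the outcome as defined is a subtraction. It cannot be computed for a patient who dies before the day-7 or discharge examination, although death is the worst result.

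At stake is the precision of one clinical signal in a trial whose size was set by recruitment capacity and whose results are meant to inform a later trial.

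**Working it through.** **Inputs.** From the article: 25 per group, raw change as outcome, two-sample tests, no admission NIHSS covariate. Not in the article, so assumed over a range: the admission to day-7 correlation r, the ratio k of day-7 SD to admission SD, and the early death rate. The article states no power or precision figure for NIHSS. Its figures of 177 per group, 18% and 65% concern infarct growth and do not bear on this point.

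**Step 1: equal SDs (k = 1).** In units of the day-7 variance, the per-patient variance behind the treatment contrast is 2(1 − r) for the change score and 1 − r² for linear ANCOVA. The ratio ANCOVA/change is (1 − r²)/[2(1 − r)] = (1 + r)/2. The last column is 25 × (1 + r)/2, the number per group under ANCOVA that matches 25 per group with raw change.

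| r | Change | ANCOVA | Ratio | Variance cut | 25 per group is worth |
|---|---|---|---|---|---|
| 0.3 | 1.40 | 0.91 | 0.65 | 35% | 16.2 |
| 0.5 | 1.00 | 0.75 | 0.75 | 25% | 18.8 |
| 0.6 | 0.80 | 0.64 | 0.80 | 20% | 20.0 |
| 0.7 | 0.60 | 0.51 | 0.85 | 15% | 21.2 |
| 0.8 | 0.40 | 0.36 | 0.90 | 10% | 22.5 |
| 0.9 | 0.20 | 0.19 | 0.95 | 5% | 23.7 |

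**Step 2: unequal SDs.** In units of the admission variance, the change score has k² + 1 − 2rk and ANCOVA has k²(1 − r²). The difference is 1 − 2rk + r²k² = (1 − b)², with slope b = rk. The loss is therefore never negative and disappears at b = 1.

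| k | r | b | Change/ANCOVA |
|---|---|---|---|
| 0.8 | 0.5 | 0.40 | 1.75 |
| 0.8 | 0.7 | 0.56 | 1.59 |
| 1.2 | 0.5 | 0.60 | 1.15 |
| 1.2 | 0.7 | 0.84 | 1.03 |
| 1.5 | 0.5 | 0.75 | 1.04 |
| 1.5 | 0.7 | 1.05 | 1.00 |

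These are large-sample formulas. Estimating the slope from 50 patients costs a factor of about 1 + 1/(50 − 4) = 1.02, so the net gain is slightly smaller.

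**Step 3: chance imbalance.** The difference in mean admission NIHSS between groups has standard error √(2/25) = 0.28 admission SDs. A difference d shifts the expected difference in change by (b − 1)d. At b = 0.6, 40% of the imbalance remains, with reversed sign: 0.4 × 0.28 = 0.11 SD for a one-standard-error imbalance. At b = 1 nothing remains.

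**Step 4: deaths before the assessment.** At assumed rates of 2%, 5% and 10%, the expected number among 50 is 1, 2.5 and 5. The chance of at least one is 1 − 0.98⁵⁰ = 64%, 1 − 0.95⁵⁰ = 92% and 1 − 0.90⁵⁰ = 99.5%.

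As an illustration of what leaving them out would do, assume admission mean 14 and SD 6, day-7 mean 9 and SD 7, r = 0.6, deaths concentrated among the worst patients, and no treatment effect on NIHSS. A simulation with 10% against 5% early deaths moves the difference by about 0.26 points in favour of the arm with more deaths. The change-score SD is √(36 + 49 − 2 × 0.6 × 42) = √34.6 = 5.9, and the standard error with 25 per group is 5.9 × 0.28 = 1.7. The shift is thus about 0.16 standard errors.

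**The case against.** Several defences have force.

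- **The change score is a legitimate estimator.** Under randomization it is unbiased, and it already subtracts the baseline. A reader might infer that an admission imbalance passes whole into the result; only the share (1 − b) does. This stands: the issue is precision, and bias only conditional on an observed imbalance.
- **The size is not established.** The article gives no NIHSS SD or correlation, and some plausible combinations give no loss at all. The formula is for linear ANCOVA; no gain has been computed for a rank-based or ordinal analysis, or against the Mann-Whitney test that the article also allows. This stands.
- **The analysis is not wholly unadjusted.** Adjustment for recanalization is scheduled. True, but it leaves the use of admission NIHSS untouched.
- **The amendments did not create the difficulty.** Improvement was already capped by the admission score under the limits of 4 to 25. This stands; lifting the limits only permits a wider range.
- **Death.** A reader might infer that the comparison is among survivors only and that the arm with more early deaths will look better. The article does not say this. No exclusion is written, and a rule for death may sit in the full protocol or the SAP, which are not shown. Death is also captured by the 3-month mRS. What remains is narrower: the difference as defined has no value for such a patient.

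Nothing here shows a fault in the mRS analysis.

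**Conclusion.** The point holds in a limited form. The article fixes the first clinical outcome as a raw NIHSS difference, compares it by two-sample tests, and names only recanalization success for adjustment. Using admission NIHSS as a covariate would generally be more precise, and would remove the part of any chance admission imbalance that subtraction leaves behind.

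With equal SDs assumed, the variance falls by about 10% to 25% for correlations of 0.8 to 0.5. It could fall by more if the slope is well below 1, and by little or nothing if the slope is near 1. None of these inputs comes from the documents.

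The documents do not support a claim of bias from the change score, or a claim that patients who die are excluded. The weight is minor: this is a secondary outcome of a 50-patient pilot that describes itself as underpowered and whose main aim is to estimate the reduction in infarct growth.

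**What to change.** Compare NIHSS at day 7 (or at earlier discharge) between groups with admission NIHSS as a covariate: ANCOVA, on ranks or through an ordinal model if the scores are skewed. Keep the raw change from admission as a descriptive summary. State that a patient who dies before the assessment takes the worst rank in this analysis.

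The cost is a few sentences in the analysis plan. Admission NIHSS is already collected, and no extra patients or visits are needed. The small downside is that an adjusted or rank-based contrast is less direct to read than a difference in points, which is a reason to keep the raw change alongside it.

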In order to inform sample size and power calculations, we have used unpublished data from 200 consecutive patients who underwent mechanical thrombectomy for acute ischemic stroke in our institution and for whom infarct growth between admission and 24 h follow-up imaging was estimated using the method described in section Primary Outcome (voxel-wise infarct growth on DWI). These data were used to confirm the log-normal distribution of infarct growth and to provide the expected median and SD for the control group of STICA, namely 16 and 48.8 ml, respectively. Using the method described by O'Keeffe et al. (41), and assuming a 30% relative reduction in median infarct growth in the treatment group, 177 patients per group would be needed (two-sided comparison of untransformed medians, alpha = 5%, beta = 20%). Based on this effect size, a sample size of 25 patients per group would yield a statistical power of 18%. Conversely, with 25 patients per group, the effect size that could be detected with a statistical power equal to 80% would be a 65% relative reduction in infarct growth. Such an effect size may seem overly optimistic but the main aim of this pilot study is to provide a reasonable estimate of infarct growth reduction with cathodal tDCS, in order to inform the sample size calculation for, and feasibility of a multicenter phase IIb or phase III superiority trial.

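### The severity subgroup splits an already recorded NIHSS score at the trial's own median, which loses roughly a quarter to two-fifths of its information on a severity-by-treatment trend

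*Protocol article*

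**What the plan says.** In the protocol article, Secondary outcomes, the second planned stratification compares "patients with NIHSS admission score above vs. below the median NIHSS admission score". The text gives no numerical cut, no interaction test and no use of NIHSS as a score for this subgroup. The other three stratifications rest on criteria set in advance: perfusion–diffusion mismatch (Tmax above 6 s, ratio above 1.8), recanalization (TICI 2b or 3 on arteriography), and initial large vessel occlusion.

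Under Statistical analysis, "The inclusion of 50 patients is planned over 30 months", with 25 per group. The same section says the number was not formally calculated and that the trial will most likely be underpowered. Its main aim is to estimate the reduction in infarct growth for a later trial. Infarct growth is taken as log-normal.

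Under Inclusion and exclusion criteria, the NIHSS range was initially 4 to 25. Amendments then opened the trial to all eligible patients "irrespective of the NIHSS score" and irrespective of the revascularization procedure.

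**The concern.** NIHSS is an ordered score with many values. A median split treats patients just either side of the cut as different in kind, and all patients on one side as alike. If the effect of stimulation varies smoothly with severity, the split estimates that variation less precisely than the score does. In a 50-patient trial there is little precision to spare.

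The cut is also a product of enrolment. Eligibility was widened during the trial, and thrombectomy was extended to the 6 to 24 h window from 27 June 2018, so the median partly reflects when patients were recruited. A later trial would learn more from the effect at stated NIHSS values than from the effect in two halves of this sample.

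**Working it through.** **1. The plan's own figures.** None concerns the NIHSS subgroup, but the sample-size statement sets the scale. Inputs from Statistical analysis: control median and SD "namely 16 and 48.8 ml, respectively"; two-sided alpha 5%; power 80%; 30% reduction in the median (16 to 11.2 ml).

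- Log variance from median m and SD: s² = ln{[1 + √(1 + 4(SD/m)²)]/2}. Holding the raw SD at 48.8 ml in both arms, s² = 1.278 for m = 16 and 1.586 for m = 11.2.
- n = (1.960 + 0.842)² × (1.278 + 1.586)/(ln 0.7)² = 176.7, so 177 per group.
- Power at 25 per group: Φ(0.357/√(2.865/25) − 1.960) = Φ(−0.906) = 18%.
- 65% reduction (m = 5.6, s² = 2.222): Φ(1.050/√(3.501/25) − 1.960) = Φ(0.846) = 80%.

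All three stated figures reproduce. The subgroup definition does not enter any of them.

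**2. Information lost by the split.** For an effect that changes linearly with the score X, a two-group version of X keeps a share r² of the information, where r is the correlation of X with the group indicator. The loss is 1 − r². For a normal X split at its median, r² = 2/π = 0.637, so the loss is 36.3%. For this one analysis that is like leaving out 0.363 × 50 ≈ 18 patients.

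The protocol article gives no NIHSS distribution, so everything below is assumption.

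- In simulated trials of 50, r² was 0.66 (rounded normal, mean 12, SD 6.5), 0.58 (gamma, mean 9, SD 6.5) and 0.75 (uniform, 4 to 25). The losses are 34%, 42% and 25%.
- A second set of rounded distributions, with patients at the median placed on one side or the other:

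| Assumed score | Loss |
|---|---|
| Normal, mean 12, SD 6 | 35% |
| Normal, mean 15, SD 6 | 36% |
| Normal, mean 8, SD 4 | 35% |
| Gamma, mean 12, SD 7 | 39% to 42% |
| Gamma, mean 8, SD 6 | 41% to 46% |
| Gamma, mean 5, SD 4 | 43% to 51% |
| Uniform, 4 to 25 | 25% |

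The highest losses need a low, strongly skewed score. The lowest needs a flat score over the initial eligibility range, which was later dropped.

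**3. What this does to power.** Take an interaction that the continuous score would detect with 80% power (standardised effect 1.960 + 0.842 = 2.802). The split reduces it to 2.802 × √r²:

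- r² = 0.75: Φ(2.426 − 1.960) = 68%
- r² = 0.637: Φ(2.235 − 1.960) = 61%
- r² = 0.58: Φ(2.134 − 1.960) = 57%

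These figures compare two methods. They do not forecast this trial's power for an interaction.

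**4. The reverse case.** If the effect truly steps at the median, the same r² applies with the roles exchanged: the split is the right model and the continuous term loses the 25% to 42%.

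**The case against.** A median split is a common descriptive choice for an exploratory subgroup in a pilot. No decision depends on this one, the article does not plan a severity trend, and it nowhere claims that effect modification is linear in NIHSS. The loss is therefore measured against an analysis that the authors did not promise, under distributions that they did not give. All of this stands, and it limits the point to an improvement rather than an error. It does not make the split the better method: the score is already collected, and a smooth change with severity is at least as plausible as a step at whatever median this sample produces.

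A reader might infer three stronger things that the article does not support.

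- *That patients scoring exactly the median are excluded.* The text states no exclusion, and which side takes them is a detail ordinarily left to the analysis plan. With an even 50 patients the median can also fall between two integers: nobody sat on it in 17% to 39% of simulated samples, depending on the assumed shape.
- *That ties cause the loss of about a third.* They do not. The loss belongs to any median split, and placing ties on one side does not recover it.
- *That the groups cannot be reproduced.* Once the median is reported, a later trial can use it as a cut. The fair complaint is that its value is set by enrolment.

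**Conclusion.** The point holds as a cheap improvement to an exploratory analysis. Splitting admission NIHSS at the trial's own median loses roughly a quarter to two-fifths of the score's information on a linear severity-by-treatment trend: 36% for a normal score, and up to about half if scores are low and strongly skewed. The size rests on assumed NIHSS distributions and on effect modification that is roughly linear on the analysis scale. It concerns this subgroup only and leaves the intention-to-treat primary analysis and the sample-size figures untouched. A continuous interaction would not make the subgroup well powered in 50 patients; it would only use the available data better.

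**What to change.** Make the main form of subgroup (ii) a treatment-by-admission-NIHSS interaction with NIHSS continuous, including all randomised patients with the needed data. Fit it on log infarct growth or another scale suited to the log-normal outcome, and state how a growth of zero is handled if logs are used. Report the estimated treatment effect with its interval at two or three NIHSS values fixed before unblinding and lying within the range of scores enrolled. Keep the median split, if wanted, for display only, and label the whole analysis exploratory.

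The cost is a sentence or two in the analysis text and no new data. The downside is the linearity assumption, to be checked with a plot of outcome against NIHSS by arm, and lower power than the split if the effect really does step at the median.
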